## Abstract

**Background:**

Several Internet-based interventions for eating disorders have shown their effectiveness. Still, there is a need to refine such interventions given that most existing programs seem to be limited by their static ‘one-size-fits-all’ approach. ‘Featback’, an Internet-based intervention for symptoms of eating disorders provides a more individualized approach. It consists of several components (psychoeducation, a fully automated monitoring and feedback system, and support from a coach), which can be matched to participants’ needs and preferences. Until now, it is unclear whether online self-help interventions for eating disorders with support are more effective than those without. The aims of the current study are i) to examine the relative effectiveness of (the different components of) Featback; ii) to examine predictors, moderators and mediators of intervention responses; iii) to report on practical experiences with Featback; and iv) to examine the cost-effectiveness of Featback.

**Methods/design:**

Individuals aged 16 years or older, with mild to severe eating disorder symptoms will be randomized to one of the four study conditions. In condition one, participants receive the basic version of Featback, consisting of psychoeducation and a fully automated monitoring and feedback system. In conditions two and three, participants receive the basic version of Featback supplemented with the possibility of infrequent (weekly) or frequent (three times a week) e-mail, chat, or Skype support from a coach, respectively. The fourth condition is a waiting list control condition. Participants are assessed at baseline, post-intervention (8 weeks), and at 3- and 6-month follow-up (the latter except for participants in the waiting list control condition). Primary outcome measures are disordered eating behaviors and attitudes. Secondary outcome measures are (eating disorder-related) quality of life, self-stigma of seeking help, self-esteem, mastery and support, symptoms of depression and anxiety, repetitive negative thinking, motivation to change, user satisfaction, compliance, and help-seeking attitudes and behaviors.

**Discussion:**

This study aims to provide more insight into the (cost-) effectiveness of Internet-based interventions for eating disorders, particularly those with and without professional support, as well as different levels of support.

**Trial registration:**

NTR3646

## Background

Despite the disabling nature of mental disorders, many individuals with mental health problems do not receive treatment [1]. Suggested reasons for this treatment gap include stigma, embarrassment, lack of recognition of symptoms, and preference for self-reliance [2,3]. New technologies can possibly bridge the gap between the need and the actual received treatment, by providing ways to reach individuals who are otherwise hard to reach. For example, the anonymity of Internet-based interventions can decrease barriers that exist in more intensive face-to-face treatment. Internet-based interventions also offer other advantages over traditional face-to-face interventions, such as cost-effectiveness and widespread dissemination. Accessibility and convenience can be enhanced as Internet-based interventions are available 24 hours a day and can be accessed at any place. It is not surprising that the field of e-mental health is rapidly growing: more and more Internet-based interventions for mental disorders have been developed and investigated over the past years. Numerous programs have proven to be effective, particularly in preventing and reducing symptoms of depression and anxiety [4-6].

In the field of eating disorders (ED), a recent review demonstrated the superiority of Internet-based therapy over waiting lists for the reduction of ED psychopathology, the frequency of binge eating and purging, and also for the improvement of (ED-related) quality of life [7]. Regarding the preventive intervention of ED, numerous studies have evaluated an Internet-based intervention called ‘Student Bodies’ [8-15], consisting of psychoeducation, a web-based body image journal (allowing participants to monitor events that trigger body image dissatisfaction), and an online asynchronous discussion group. A meta-analytic review [16] demonstrated ‘Student Bodies’ to be effective in reducing ED-related attitudes, such as weight and shape concerns and a negative body image.

The evaluation of the necessity and importance of adding more personalized levels of support is important as it is associated with an increase in costs and may furthermore limit the availability of the intervention, given the need for a sufficient number of coaches. Nevertheless, providing personalized support seems to be beneficial: studies in the field of depression and anxiety suggest that Internet-based interventions with support are more effective than those without [4,6]. However, the degree of provided support varies considerably and the most adequate quantity of support in order to achieve positive effects of an intervention is yet unknown. Two Internet-based intervention studies, one for social phobia [20] and one for panic disorder [21], failed to identify an incremental effect of more frequent levels of support, although both studies had small sample sizes. Tate et al. [22] compared e-mail counseling, computer-automated tailored counseling, and no counseling in an Internet weight loss program. After six months, participants in the e-mail counseling group achieved significantly greater weight loss than participants in the computer-automated feedback. Given these mixed results on the necessity and importance of personalized support, the current study could help to gain more insight in the potential incremental effects of different levels of support on the effectiveness of an intervention.

This randomized controlled trial will compare four conditions: i) a basic version of Featback consisting of psychoeducation and a fully automated monitoring and feedback system; ii) same as (i), but supplemented with the possibility of infrequent, weekly e-mail, chat or Skype support from a coach; iii) same as (i), but supplemented with the possibility of frequent (three times a week) e-mail, chat or Skype support from a coach; and iv) a waiting list control condition (WLC). The WLC could be regarded as a care-as-usual condition, given that all participants are free to undergo any other intervention. The three active intervention conditions are developed in a stepped-care framework, starting with the least intensive intervention and moving up to (the possibility of) more intensive components. Participants are assessed at baseline (T0), post-intervention (T1: 8 weeks), and at 3- (T2) and 6-month follow-up (T3). Participants in the WLC condition will not be measured at T3, as they will be offered the intervention of condition two after T2.

The primary aim of the current study will be to investigate the effectiveness of (the different components of) Featback. The second aim is to investigate potential predicting, moderating, and mediating variables in order to gain insight into when or for whom this intervention works, as well as how it works. The third aim of this study is to report on the practical experiences of Featback, such as the user satisfaction and the (intensity of) use of the different components. Finally, the fourth aim of this study is to examine the cost-effectiveness of Featback.

## Methods

### Design

This study is a randomized control trial including three active intervention conditions and a waiting list control condition (for more details: see Study conditions). Ethical approval has been obtained by an independent medical ethics committee (CCMO no. NL40085.058.12).

### Sample

Inclusion criteria will be deliberately kept broad, given that we aim to reach a broad population of individuals with ED. Participants will have to: i) be sixteen years of age or older; ii) report at least mild ED symptoms (as assessed by the Short Evaluation of Eating Disorders (SEED) [23]) or show at least some risk for the development of an ED (as defined by scoring 40 or higher on the Weight Concern Scale (WCS) [24]); and iii) have access to a computer, iPhone, iPad, Smartphone or laptop with an Internet connection. Regarding the second criterion (reporting at least mild ED symptoms), individuals need to report at least one of the following symptoms: a BMI of 18.5 or less, self-induced vomiting, binge eating episodes, excessive exercise or use of laxatives for at least once a week over the past four weeks, or a body distortion showing that one’s estimated BMI is at least two points higher than one’s actual BMI.

### Procedure and randomization

Participants will be recruited through advertisements on websites (among others Proud2Bme (http://www.Proud2bme.nl)), and/or academic schools, magazines, newspapers, health care centers, and patient unions. Interested individuals can apply for participation by sending an e-mail to the researcher, who will send them an information letter and invite them to complete an online informed consent and screening questionnaire. After completion, individuals receive an e-mail with feedback on the severity of their ED symptoms, and those who meet the inclusion criteria will be invited to complete the baseline questionnaire for the study. After completion of the baseline questionnaire, participants will be randomized to one of the four study conditions and will be notified by e-mail. The randomization allocation will be conducted by an independent researcher, who will create random-number tables by means of SPSS. Randomization will take place in blocks of 40 participants. The number of participants (n = 10) in each block will be equal for the four conditions. The allocation sequence will be concealed from the main researcher involved in the enrolment and assignment of participants, thus preventing foreknowledge of the intervention assignment.

### Study conditions

#### Basic featback

Participants will receive access to the website of Featback (http://www.Featback.nl) where comprehensive information on ED can be found (e.g., psychoeducation). In addition, participants will have access to a monitoring and feedback system. On a weekly basis, participants will receive an e-mail inviting them to complete a monitoring questionnaire. This monitoring questionnaire consists of eight items assessing cognitive and behavioral correlates of four dimensions: i) body dissatisfaction; ii) excessive concern with body weight and shape; iii) unbalanced nutrition and dieting; and iv) binge eating and compensatory behaviors. Answers can be given on a 4-point Likert scale. After completion of the monitoring assessment, feedback messages are automatically generated according to a pre-defined algorithm. The feedback messages are individually tailored. That is, they are based on the functionality of reported ED-related attitudes and behaviors (functional versus dysfunctional), as well as patterns of change (improved, deteriorated or unchanged). For detailed information about the feedback algorithm, see Bauer et al. [17]. Subsequently, the generated feedback is sent to the participants using Web-Akquasi data management software [25]. In case of severe ED symptoms, action is taken (see ‘Ethical precautions and crisis management’ for more details).

#### Basic featback + infrequent support

Participants will receive the basic Featback intervention as described above, supplemented with the possibility of infrequent (weekly) e-mail, chat or Skype support from a coach.

#### Basic featback + frequent support

Participants will receive the basic Featback intervention as described above, supplemented with the possibility of frequent (three times a week) e-mail, chat or Skype support from a coach.

#### Waiting list control condition (WLC)

Participants in this condition will be assigned to a waiting list, for the purpose of providing a comparison group for the active intervention conditions. Participants will be offered the intervention of condition two after a waiting period of five months (T2).

### Support from a coach

Participants will be able to schedule support sessions through different mediums: e-mail, chat or Skype. Coaches will be instructed to e-mail participants in case participants do not schedule any appointments or in case participants do not show up at scheduled support sessions, and to repeat this process twice per non-response. Chat and Skype sessions will imply 20 minutes with a coach. An e-mail session will contain one reply by e-mail from the coach to the participant (who will be instructed to e-mail his/her coach beforehand). The methodology of chat sessions is based on a 5-phase model, containing i) a warm welcome, ii) clarifying of the question, iii) determining the goal of the conversation, iv) concrete elaboration of the goal of the conversation, and v) closing the circle. More detailed information on this model can be found in the handbook written by Schalken et al. [26]. E-mail support is based on the following phases: i) extracting the question, ii) formulating an answer, and iii) checking/re-reading the message and sending it. All coaches will follow an intervention protocol that includes all guidelines for the provision of support.

Support will be provided by master level students in clinical psychology or individuals with a degree in the field of psychology. All coaches will undergo an intensive two-day training from an external company (‘Stichting E-hulp’), specifically focused on the delivery and methodology of online support. Coaches will be taught the basic principles for delivering online support and they will practice with case materials throughout the training. Monthly face-to-face supervision sessions will be organized by the main researcher, a psychologist and an experienced psychotherapist as a matter of routine professional and ethical care, as well as to reinforce adherence to the protocol. Individual supervision will also be provided to all coaches during their first month as online coach. Hereafter, the support sessions between coaches and participants will be regularly checked at random. A forum, in the form of a secured Facebook community, will be available for questions and discussion of scenarios in between the face-to-face supervision sessions, and coaches will furthermore be free to contact the supervisors at any time.

### Ethical precautions and crisis management

Coaches are instructed to refer participants who report suicidal ideation to the website 113Online (http://www.113online.nl); this organization aims to prevent suicide. It employs psychologists, psychiatrists, and a large group of fully trained volunteers, who are accessible via telephone and chat day and night. Furthermore, action is taken when screening or monitoring data show that a participant’s BMI is equal or lower than 15 or when a participant reports being engaged in self-induced vomiting, binge eating or use of laxatives at least once a day over the past four weeks. Subsequently, in case a participant is in condition one (basic Featback) or four (WLC, only screening data), the Featback team will send an e-mail with the message that his/her test scores indicate severe ED symptoms and that if he/she is not yet in treatment, we strongly recommend seeking professional help. In case a participant is in condition two or three, the Featback team will check whether one or more support sessions are planned for the week, and if not, will contact the participant with the message that we believe that his/her test scores indicate severe ED symptoms and that we strongly recommend to make use of one or more support sessions. In these support sessions, the alarm signals will function as a starting point for the conversation and participants will be stimulated to seek professional help. In case participants do not sign in for any support session during the week, the Featback team will send an e-mail as described for participants in condition one.

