#### Assessments

All assessments are self-reported and will be conducted online. Table 1 depicts an overview of the assessment instruments that will be used throughout each stage of the study. Primary outcome measures are disordered eating behaviors and attitudes (SEED, EDE-Q) [23,27]. Secondary outcome measures contain ED-related quality of life (ED-QOL) [28], self-stigma of seeking help [29], self-esteem, mastery and support [30], symptoms of depression and anxiety (PHQ-4) [31], repetitive negative thinking (PTQ) [32], motivation to change [33,34], and user satisfaction, as well as compliance and help-seeking attitudes and behaviors. Cost-effectiveness will be evaluated by means of the reported quality of life (EQ-5D) [35] and medical and societal costs (Trimbos/iMTA Questionnaire for Costs Associated with Psychiatric Illness: TiC-P) [36].

**Table 1 T1:** Overview of the assessment instruments used throughout each stage of the study

**Assessment**	**Screening**	**T0: Baseline**	**Weekly monitoring: even weeks**	**Weekly monitoring: uneven weeks**	**T1: Post-intervention**	**T2: 3-month follow-up**	**T3: 6-month follow-up**^2^
Weight Concern Scale (WCS)	X	-	-	-	-	-	-
Short Evaluation of Eating Disorders (SEED)	X	X	-	-	X	X	X
Short Evaluation of Eating Disorders II (SEED-II)	-	-	X	X	-	-	-
Demographics and other information	-	X	-	-	-	-	-
Monitoring questionnaire	-	-	X	X	-	-	-
Patient Health Questionnaire 4 (PHQ-4)	-	X	-	X	X	X	X
Perseverative Thinking Questionnaire (PTQ)	-	X	-	X	X	X	X
Eating Disorder Examination Questionnaire (EDE-Q)	-	X	-	-	X	X	X
Self-stigma of seeking help	-	X	-	-	X	X	X
Self-esteem, mastery and support	-	X	-	-	X	X	X
Eating Disorder-related Quality of Life (ED-QOL)		X	-	-	X	X	X
Motivation to change	-	X	-	-	X	X	X
Session Rating Scale (SRS)	-	-	X^1^	-	-	-	-
User satisfaction questionnaire	-	-	-	-	X^2^	-	-
Attrition follow-up question	-	-	X^3^	X^3^	X^3^	X^3^	X^3^
Help-seeking attitudes and behavior questionnaire	-	-	-	-	X	X	X
Quality of life (EuroQol: EQ-5D)	-	X	-	-	X	X	X
Trimbos/iMTA questionnaire for costs associated with psychiatric illness	-	X	-	-	X	X	X

^1^Only asked after participants’ first week of participation.

^2^Not sent to participants who are randomized to the waiting list control condition.

^3^Sent to participants who fail to complete the monitoring assessment, or the T1, T2 or T3 assessment, respectively.

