### Short Evaluation of Eating Disorders (SEED)

The SEED [23] is a brief self-report measure for the assessment of key ED symptoms. It assesses the three main symptoms of anorexia nervosa (degree of underweight, fear of weight gain, and distortion of body perception) and bulimia nervosa (amount of binge eating, amount of compensatory behavior, and over concern with body shape and weight). Total severity indexes can be calculated for each of the two diagnoses (range 0–3), with higher scores reflecting higher severity indexes. The behavioral measures (bingeing, excessive exercising, and compensatory behaviors) are assessed over the previous four weeks. The SEED has demonstrated construct validity and criterion-related validity, and was furthermore shown to be sensitive to symptom change [23].

Given that the SEED will be administered every week during the intervention period as well, the four-week timeframe for the behavioral measures is adapted to a timeframe of one week. This adapted questionnaire will be referred to as SEED-II.

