### Attrition follow-up questions

According to Eysenbach [43], there are two different processes of attrition; “dropout attrition” refers to participants being lost to follow‒up, thus not returning follow‒up questionnaires and “non-usage attrition” refers to participants who stop using the intervention. To be able to investigate the reasons for both dropout and non-usage attrition, two attrition follow-up questions are designed: one in case participants fail to complete monitoring assessments and another one in case participants fail to complete the T1, T2, or T3 assessment.

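### As written, the severe-symptom alarm ignores SEED answers at T1 in the waiting list and at T2 and T3 in the active arms, although they can meet its own thresholds

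*Protocol article*

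**What the plan says.** The section on ethical precautions and crisis management defines a state that calls for action: a BMI of 15 or lower, or vomiting, bingeing or laxative use at least daily over four weeks. It names the data that are read: "action is taken when screening or monitoring data show that" the threshold is met. The response depends on the arm. Basic Featback and the waiting list get an e-mail recommending professional help. The two coached arms are first steered to a support session and get that e-mail if they do not sign up. For the waiting list the source carries an explicit limit: "four (WLC, only screening data".

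The section on basic Featback introduces monitoring as a weekly activity: "On a weekly basis, participants will receive an e-mail inviting them to complete a monitoring questionnaire". The SEED section ties the weekly version of that instrument to the programme period: "Given that the SEED will be administered every week during the intervention period as well". Of the full SEED it says: "The behavioral measures (bingeing, excessive exercising, and compensatory behaviors) are assessed over the previous four weeks". Table 1 schedules the full SEED at screening, T0, T1, T2 and T3, with no T3 in the waiting list. On the wait itself: "Participants will be offered the intervention of condition two after a waiting period of five months (T2").

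**The concern.** The trial decides in advance which answers are serious enough to act on, and then, as worded, reads only some of the assessments that contain those answers. Two groups fall outside. One is waiting-list participants who get worse after screening: T1 is the only SEED they complete between baseline and the end of the wait, and it is not read. The other is active-arm participants who deteriorate or relapse in the six months after weekly monitoring stops.

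Participants may be as young as 16, severity has no upper limit at entry, and nobody is seen face to face. The article describes no contact with the waiting list through which deterioration would be noticed other than online self-report. A trial that holds an answer meeting its own alarm definition and does nothing has a badly set safety rule, even where the prescribed action is modest.

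**Working it through.** No power or alpha figure is involved. The check compares the alarm rule with the schedule and then counts the assessments outside the rule.

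**1. Does monitoring include T1, T2 or T3?** No.
- The section on attrition questions plans two separate questions: "one in case participants fail to complete monitoring assessments and another one in case participants fail to complete the T1, T2, or T3 assessment".
- Footnote 3 of Table 1 makes the same split: "Sent to participants who fail to complete the monitoring assessment, or the T1, T2 or T3 assessment, respectively". Table 1 also gives weekly monitoring its own columns.
- The waiting list completes T1 and T2. If those counted as monitoring, limiting that arm to screening data would remove data the arm does supply. A broad reading therefore conflicts with the bracket, unless the bracket is itself a deliberate exclusion, and then the waiting-list gap is intended and explicit.

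**2. Can the unread answers support the alarm?** Yes. At screening only the WCS and the SEED are given, and the sample section uses BMI and the behaviours, as assessed by the SEED, for eligibility. The screening alarm must therefore rest on the SEED. The same instrument, with the same four-week window for behaviours, returns at T1, T2 and T3. The weekly SEED-II has a one-week window and fits the four-week threshold less well.

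**3. Timing.** T1 is at 8 weeks, T2 at about 5 months (8 weeks + 3 months, in line with the five-month wait), and T3 at about 8 months (8 weeks + 6 months).
- The four-week windows at T2 and T3 cover roughly months 4–5 and 7–8, wholly after weekly monitoring has ended.
- The waiting list has no alarm check between screening and T2.
- Example: a waiting-list participant with BMI 17 at screening and 14.5 at T1 is over the threshold at T1 and is sent nothing until T2, three months later.

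**4. Count.** From the sample size section: 86 per group, so 86 in the waiting list and 3 × 86 = 258 in the active arms.

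| Assessment | Scheduled | Returned at 70% |
|---|---|---|
| Waiting list T1 | 86 | 60.2 |
| Active T2 and T3 | 258 × 2 = 516 | 361.2 |
| Total outside the alarm | 602 | 421.4 |

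The returned assessments come from 60.2 + 180.6 = 240.8 people if the same active participants answer T2 and T3, and from at most 60.2 + 258 = 318.2 if they differ.

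**5. What is left out of the count.** Active T1 (258 × 0.7 = 180.6 returned) falls inside the weekly SEED-II period, so the gap there is mainly participants who skipped monitoring. At T2 the waiting list (86 × 0.7 = 60.2 returned) is offered condition two, so the gap there is those who decline it. Both are largely covered.

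**The case against.** **The article is a condensation.** Only the waiting-list limit is explicit. The active T2 and T3 assessments are 516 of the 602 (86%), and no sentence says that nothing is done with them. Crisis procedures may be fuller in the approved protocol or in the coaches' guidelines, neither of which is shown. This stands as a caveat, and the finding is about the rule as written. But the article states the rule and its data sources; it does not merely leave them out.

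**Monitoring data could be meant loosely.** The eight-item weekly questionnaire does not list BMI among its dimensions, and the SEED-II looks back one week, so the four-week threshold sits awkwardly with weekly data. That is true, but the article's own usage and the waiting-list bracket both favour the narrow meaning.

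**The waiting list stands for care as usual.** A help-seeking message at T1 could raise outside care and narrow the T2 differences in help-seeking and cost, and T2 is the last comparison with that arm. This is a real cost. It is not a new principle, because severe waiting-list cases already get the same e-mail at screening, and under the fix all arms would get the same message from T1.

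**The harm is small and unquantified.** The missing action is one advisory e-mail to people who know they have symptoms and who received feedback on severity at screening. The counts describe the schedule, not severe cases. The BMI example is extreme: (17 − 14.5)/17 is about a 15% loss in roughly eight weeks. All of this is fair. It limits the weight of the point without removing it.

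**Conclusion.** The concern holds. Followed literally, the alarm leaves 602 scheduled SEED assessments unread for safety: 86 at T1 in the waiting list and 516 at T2 and T3 in the active arms. About 421 would be returned, by some 241 to 318 people. These figures use the planned group sizes and assume that the protocol's 30% dropout applies equally at each time point. They are upper bounds on opportunities to act; nothing in the document allows an estimate of how many would cross the threshold. Severe cases at screening in every arm, and during weekly monitoring in the active arms, are covered.

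No primary estimate, test or sample size is affected. The point should be fixed because it concerns patient safety and is cheap to correct. Confidence is moderate, since the full protocol may already extend the rule.

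**What to change.** Apply the existing thresholds to the SEED at T1 and T2 in all four arms and at T3 in the active arms. Two wording changes in the crisis management section are enough: name screening, monitoring, T1, T2 and T3 as data sources, and for the waiting list replace screening alone with screening, T1 and T2.

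From T1 on, send every arm the e-mail now used for basic Featback, since the 8-week programme and its coach support have ended. For the waiting list at T2, send it together with the offer of condition two. Log each message by arm and time point, and report the counts beside the T2 help-seeking and cost-utility results. Thresholds and e-mail content stay as they are.

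The cost is an automated check on data already collected online, a log and a few e-mails. The downside falls on T2: its cost questionnaire looks back three months, which is the T1–T2 interval, so any care prompted by a T1 message is counted there. At most the roughly 60 waiting-list participants who return T1 could be messaged, and only those over the threshold. The primary comparison is safe because T1 is completed before any T1 message goes out. Enrolment closed on 17 June 2013, so the change helps only assessments still outstanding. If the full protocol already reads T1 to T3, a sentence saying so is sufficient.
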